### Participant timeline {18}

A schematic diagram of participant enrollment, interventions, assessments, and visits for participants is presented in Fig. 3. Each participant is involved for approximately 9 months (12 weeks intervention and 6 months follow-up period) (see Fig. 3). As a standard procedure, and according to national stroke guidelines, all patients with dysphagia in the acute phase of stroke are followed up with a FEES at 1–3 months after stroke onset. If persistent dysphagia is present, the patient is invited to participate in the study. After their written informed consent is obtained, the participant will be allocated to either intervention or control group. Based on the baseline FEES assessment (performed prior allocation, as part of routine procedure), the participant will receive individualized compensatory strategies. Assessments regarding secondary outcomes will be conducted after the participants have given their informed consent. Same assessments as at baseline are performed after 12 weeks (end-of-treatment) and 6 months later (follow-up). The first participant was enrolled on 26 February 2022, and the final participant is expected to be enrolled in July 2028, based on an estimated annual enrollment rate of 84 participants for the remaining study period.

**Fig. 3 Fig3:**
[figure not shown]
Schedule of enrollment, interventions, and assessments. Abbreviations: EoT = end of treatment; FEES = Flexible Endoscopic Evaluation of Swallowing; MNA = Mini Nutrition Assessment; SWAL-QOL = Swallowing Quality of Life Questionnaire; mRS = modified Rankin Scale; BI = Barthel index

### Sample size {19}

Expected proportion of patients with dysphagia (i.e., DOSS ≤ 5) at follow-up in the control group is 65% [5]. We have dimensioned our study to detect a marginal odds ratio of 2 when using an ordinal proportional odds model. This corresponds to a proportion of patients with swallowing dysfunction of 52% in the intervention group. We expect a majority of patients to have a DOSS score of 5 or 6 at 12 weeks (end-of-treatment), based on clinical experience. Under the assumption of a marginal DOSS score distribution of 3%, 7%, 10%, 13%, 24%, 30%, and 13% for the DOSS score points of 1–7, respectively, 135 subjects are sufficient to detect an odds ratio of 2 with 90% power using an ordinal proportional odds regression model. Power calculations were performed using the function *popower*, from the R package Hmisc [29]. In the study, the odds ratio will be conditioned on the patients’ baseline DOSS score, as well as for the stratifying variables center and aspiration, which should provide further power compared to estimating a marginal odds ratio, as assumed in the power calculations. To account for a dropout rate of 20%, 168 patients will be recruited for each group.

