The project group has good competence, equipment, personnel, infrastructure, and ethical and regional approval to conduct the study. There is also a sufficiently large base of eligible participants. The anticipated obstacles are related to (a) dropout; therefore, the estimated power calculation is based on 90% power and risk of a 20% dropout rate, and (b) compliance in conducting clinical trials on interventions; therefore, a sensor that registers the training frequency will be attached to each oral device.

If the oral neuromuscular training intervention proves effective, it could have a substantial impact on stroke care and management. Improved swallowing function could reduce the incidence of complications like aspiration pneumonia, decrease healthcare costs, and enhance patient outcomes and quality of life. The findings may also influence national and international guidelines for treatment of post-stroke dysphagia, potentially leading to improved standards of care for stroke survivors.

The high-quality trial design, comprehensive outcome measures, and thorough consideration of potential challenges make this a well-designed study with the potential for significant clinical impact for patients with dysphagia after stroke.

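### An odds ratio of 2 from 65% dysphagia gives 48% in the intervention group, not 52%; for 65% versus 52% the design has about 70% power, not 90%

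*Protocol article*

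**What the plan says.** All of the figures stand in the Protocol article, section Sample size {19}. The control group is expected to have 65% of patients with dysphagia, defined as DOSS 5 or below. The target is then set: "We have dimensioned our study to detect a marginal odds ratio of 2 when using an ordinal proportional odds model". The next sentence translates it into a percentage: "This corresponds to a proportion of patients with swallowing dysfunction of 52% in the intervention group".

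The calculation uses a "marginal DOSS score distribution of 3%, 7%, 10%, 13%, 24%, 30%, and 13% for the DOSS score points of 1–7, respectively" and concludes that "135 subjects are sufficient to detect an odds ratio of 2 with 90% power using an ordinal proportional odds regression model". The section then allows for 20% dropout and arrives at 168 patients per group, so the 135 must be a per-group figure.

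The Interim analyses section {28b} keeps an odds ratio of 2.0 and 90% power as the target for the sample size re-estimation. The Discussion repeats that "the estimated power calculation is based on 90% power and risk of a 20% dropout rate".

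**The concern.** Under a proportional odds model the same odds ratio applies at every cut of the DOSS, including the cut that defines dysphagia. A control proportion of 65% and an odds ratio of 2 therefore fix the intervention proportion. It is not 52%.

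The percentages are the only translation of the target effect into absolute clinical terms that the protocol gives. Because the text attaches 90% power to an odds ratio of 2 and equates that odds ratio with 52%, a reader will conclude that the trial has a 10% chance of missing a 13-point reduction. If that chance is really about 30%, a null result could be taken to exclude a benefit that the trial was not sized to detect.

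**Working it through.** **Inputs, all from Sample size {19}.** Control proportion at DOSS 5 or below: 65%. Odds ratio: 2. Stated intervention proportion: 52%. DOSS distribution for scores 1 to 7: 0.03, 0.07, 0.10, 0.13, 0.24, 0.30, 0.13. Evaluable patients: 135 per group. Assumption: two-sided alpha of 0.05, which the document does not state.

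**1. Reproducing the plan's power.** The Whitehead formula for the proportional odds model, which is the form used by popower, is

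- V = n1·n2·n / [3(n+1)²] × (1 − Σp³)
- power = Φ(ln OR × √V − 1.96)

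Here Σp³ = 0.0466, so 1 − Σp³ = 0.9534. With n1 = n2 = 135 and n = 270, V = 21.29 and √V = 4.615. For an odds ratio of 2: 0.6931 × 4.615 = 3.199; 3.199 − 1.960 = 1.239; power = 89.2%. This is close to the stated 90%. A one-sided 5% test would give 94.0%, and reading 135 as the total would give 61.5%, so two-sided 5% with 135 per group is the reading that fits. The plan's numbers of patients thus follow from the odds ratio of 2.

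**2. Converting the odds ratio to a percentage.**

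- Control odds: 0.65/0.35 = 1.857
- Halved: 0.929
- Proportion: 0.929/1.929 = 48.1%, a reduction of 16.9 points

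In the other direction, (0.65/0.35)/(0.52/0.48) = 1.857/1.083 = 1.714.

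**3. Can rounding explain it?** Letting the control proportion run from 64.5% to 65.5% and the intervention proportion from 51.5% to 52.5% gives odds ratios of 1.64 to 1.79. For an odds ratio of 2 to end at 52%, the control proportion would have to be 68.4%.

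**4. Cross-check against the planning distribution.** Scores 1 to 5 sum to 3 + 7 + 10 + 13 + 24 = 57%. If this distribution is the average of two equal groups, an odds ratio of 2 implies 65.4% and 48.6%. The average of 65% and 48.1% is 56.6%; the average of 65% and 52% is 58.5%. The distribution agrees better with 48%.

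**5. Power if 65% versus 52% is the effect.** ln 1.714 = 0.5390; 0.5390 × 4.615 = 2.487; 2.487 − 1.960 = 0.527.

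| Case | OR 2 (65% vs 48%) | OR 1.714 (65% vs 52%) |
|---|---|---|
| 135 evaluable per group, fixed design | 89.2% | 70.1% |
| Same, Wilcoxon simulation, 4,000 runs | 89.2% | 69.4% |
| Same, with the efficacy look at 75% | 88.7% | 69.3% |
| All 168 per group evaluable | 94.6% | 79.3% |

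The efficacy look uses Lan-DeMets O'Brien-Fleming type critical values of 2.340 and 2.012. Over the rounding range in step 3, power at 135 per group runs from 63% to 76.5%.

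**6. Sample size for 90% power at OR 1.714.** Total N = 12 × (1.960 + 1.282)² / [(ln OR)² × 0.9534] = 455 evaluable patients, or 228 per group. Allowing for 20% dropout, 227.6/0.8 is about 285 per group.

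**The case against.** The strongest reply is that the 52% enters no calculation. The study is dimensioned on an odds ratio of 2, the power statement names an odds ratio of 2, and the re-estimation targets 2.0 again. The sentence presents 52% as derived, so this is one wrong number in an explanatory remark. The sample size, the primary model and the conduct of the trial do not depend on it, and a null result would be read mainly from the estimated odds ratio and its interval. This stands in part: if the odds ratio of 2 is the target, the sample size is sound and only the sentence changes. But the text does equate that odds ratio with 52%, so it does claim 90% power for an effect at which the design falls short.

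A second reply is that 70% is at the low end. It assumes the full 20% dropout and counts no gain from adjusting for baseline DOSS and the stratification factors. Some missing scores will also be set to 0 or imputed rather than lost. This is fair, but even with every patient evaluable the unadjusted power is 79%. The protocol expects a gain from adjustment, yet neither quantifies it nor counts it in its own figure.

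Third, the origin of the 52% is not known. It may be the complement, since 51.9% would be without dysphagia, or a 20% relative reduction, since 0.80 × 65% = 52%. The document does not say, so the sponsor has to state which effect was meant. The check against the planning distribution is likewise supportive rather than decisive, because it compares rounded planning values about 2 points apart.

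**Conclusion.** The concern holds. Starting from 65%, an odds ratio of 2 means 48% with dysphagia in the intervention group, a reduction of about 17 points; the stated 52% is a 13-point reduction with an odds ratio of 1.71. At 135 evaluable patients per group, power is 89% for the former and about 70% for the latter.

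These powers rest on a two-sided alpha of 0.05, proportional odds, the stated DOSS distribution, the planned dropout and no covariate gain. The conversion to 48% depends on none of these except the common odds ratio. The shortfall in power is real only if 65% versus 52% is the effect the trial is meant to detect; otherwise the fault lies in the stated detectable effect alone. The gap between 89% and 90%, and the cost of the efficacy look (about half a point at an odds ratio of 2), are minor.

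**What to change.** The sponsor should state which effect is intended and make the sentence agree with it.

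- **If the odds ratio of 2 is the target:** replace 52% with 48% and describe the effect as a 17-point absolute reduction. This costs one sentence and changes nothing for patients or recruitment. The stated detectable effect becomes larger, and so less favourable to the trial.
- **If 52% is the effect of interest:** restate the odds ratio as about 1.71 and the power as about 70%, or revise the sample size and the re-estimation target. Keeping 90% power would take about 228 evaluable patients per group, roughly 285 per group with 20% dropout, against 168 now.

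In the same edit, write that the 135 is per group, state the alpha and its sidedness, and give the achieved power as about 89% with the planned efficacy look included. Any other text that repeats the 52% should be changed to match. The correction should be made before the interim analyses, so that no result is interpreted against the wrong percentage.

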### Recruitment {20}

Strategies for achieving adequate participant enrollment to reach target sample size are based on (a) national recruitment of several participating hospitals/sites to ensure a large number of eligible participants; (b) environment for the assessments: portable FEES equipment is accounted for to enhance inclusion of participants with the ability to perform assessments in the patient’s own home or at a healthcare center close to the patients’ own home; and (c) person devoted to the project for inclusion, assessments, randomization, and follow-ups.

## Assignment of interventions: randomization

### Sequence generation: who will generate the sequence {21a}

The random allocation sequence was generated by the study statistician (PL), who has no involvement in participant recruitment.

### Sequence generation: type of randomization {21b}

The allocation sequence was created centrally using computer-generated random numbers stratified for center and penetration-aspiration (yes/no) according to the Penetration Aspiration Scale (PAS) [30], allocating eligible patients in a 1:1 ratio to intervention or control group. Permuted blocks with random block sizes will be used.

### Allocation concealment mechanism {22}

The allocation sequence was uploaded into the REDCap (Research Electronic Data Capture) [31] randomization module. The investigators on each site will automatically receive an allocation decision upon registering a new participant into REDCap.

### Implementation {23}

The allocation sequence was generated by study statistician and contributor to the study protocol (author PL), who is not otherwise involved in the outcome assessments or intervention. A trained investigator with multifactor authentication to access the REDCap system [31] will enroll participants. The group assignment (intervention group or control group) of each participant is retrieved from REDCap after completing baseline measurements.

## Assignment of interventions: blinding

### Who will be blinded {24a}

The evaluators (speech-language pathologist and/or otolaryngologist) responsible for assessing the primary outcome (swallowing function) will remain blinded to the trial participants’ details, including the timing of the assessment and their allocation. The biostatisticians conducting the analyses will be blinded to group allocation.

### How will be blinding be achieved {24b}

At study completion, before being assessed by evaluators, FEES recordings (video clips) will have all patient-identifiable information removed, including patient name, demographics, assessment time-point, and group allocation. These pseudonymized FEES video clips will then be placed in a random order and assigned a numerical code by a staff scientist otherwise not involved in the project. Evaluators will assess the swallow function from the FEES video recording on the DOSS scale [18, 19].

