**Methods:**

This national, multicenter, investigator-initiated, randomized, parallel-group trial compares the effect of oral neuromuscular training versus standard care in patients with post-stroke dysphagia. We will enroll 336 consecutive participants who have no prior history of dysphagia and exhibit persistent dysphagia 3 months following the onset of ischemic stroke or intracerebral hemorrhage. Participants will be randomly assigned in a 1:1 ratio to receive either a 12-week intervention consisting of standard routine care combined with oral neuromuscular training (using an oral device with sensors for adherence feedback) or current routine care alone. Standard routine care includes compensatory strategies such as bolus modification, adapted swallowing postures, and maneuvers. The primary outcome is the degree of dysphagia at end of intervention, assessed with Flexible Endoscopy Evaluation of Swallowing (FEES) by blinded evaluators, and analyzed with ordinal regression models. Secondary outcomes are changes in nutritional status, pneumonia, mortality, and quality of life after a 12-week intervention and at 6-month follow-up.

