### Interim analyses {28b}

An interim analysis is planned once 50% of participants have been assessed at end-of-treatment. At that point, an independent statistician will perform a blinded non-comparative sample size re-estimation. The updated sample size will be determined based on the observed marginal DOSS score distribution in the control group, targeting 90% power to detect a group difference at an odds ratio of 2.0, using the same sample size calculations as previously described. Because this re-estimation is non-comparative, it does not inflate the nominal type I error rate.

A second interim analysis will be conducted when 75% of the participants (according to sample size determined by the sample re-estimation) have completed the end-of-treatment assessment to evaluate efficacy. A group sequential design will be employed using the Lan-DeMets alpha-spending function with an O’Brien-Fleming type boundary. The primary ordinal regression analysis will be performed on the available data. The trial may be stopped early if the intervention shows overwhelming superiority, as determined by the boundary.

Strict operational safeguards regarding data access will be maintained throughout the study. Results of the interim analyses (both the sample size re-estimation and the efficacy calculation) will be known only to the independent statistician, while principal investigators and the study statistician will remain blinded to the results unless the independent statistician recommends stopping the trial.

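### Blinded DOSS scoring is scheduled for study completion, but both interim analyses, including the efficacy look at 75%, need DOSS scores before then

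*Protocol article*

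**What the plan says.** All references are to the protocol article.

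- **Primary outcome.** The abstract's Methods paragraph defines it as the degree of dysphagia "assessed with Flexible Endoscopy Evaluation of Swallowing (FEES) by blinded evaluators, and analyzed with ordinal regression models". Section {24a} adds that these evaluators "will remain blinded to the trial participants’ details, including the timing of the assessment and their allocation".
- **When blinded scores are made.** Section {24b}: "At study completion, before being assessed by evaluators, FEES recordings (video clips) will have all patient-identifiable information removed". It continues: "These pseudonymized FEES video clips will then be placed in a random order and assigned a numerical code by a staff scientist". Then: "Evaluators will assess the swallow function from the FEES video recording on the DOSS scale".
- **What study completion means.** The Trial status section uses the term for the end of the trial with final follow-up included, expected by the end of Q1 2029.
- **When interim scores are needed.** Section {28b}: "An interim analysis is planned once 50% of participants have been assessed at end-of-treatment". That look re-estimates the sample size from the control group's DOSS distribution. The second look comes when 75% have completed the end-of-treatment assessment, and there "The primary ordinal regression analysis will be performed on the available data". It uses a Lan-DeMets boundary of O'Brien-Fleming type and allows an early stop for superiority.
- **Other possible sources of DOSS.** Section {25a} lists DOSS among the assessments at each visit. Section {24c} calls the trial open-label, and under {22} site investigators receive the allocation through REDCap. No section says that a site-rated DOSS feeds either interim analysis.

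**The concern.** Two stated rules cannot both be followed. If the blinded scores are produced after the last follow-up visit, none exist when 50% or 75% of participants have reached end of treatment. A separate analysis plan cannot settle this alone, because it would contradict {24b} as it stands.

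The stakes differ between the looks. The 50% look makes no comparison between groups. Missing or substitute scores there could set the sample size wrongly, but they offer no route to a false claim of benefit. The 75% look is the only one that can end the trial early for superiority. If it rested on scores from raters who knew the allocation, the trial would lose its main protection against assessment bias at that decision. The interim and final statistics would then also measure different outcomes, and the alpha-spending calculation assumes that they measure the same one.

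**Working it through.** **Step 1. Timing, side by side.**

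| Event | When | Blinded DOSS scores in hand under {24b} |
|---|---|---|
| 50% look | 0.50 × 336 = 168 participants assessed at end of treatment | 0 |
| 75% look | 0.75 × 336 = 252 participants (if N is unchanged) | 0 |
| De-identification, random ordering, coding, scoring | Study completion (end of Q1 2029) | All |

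Reading study completion as each participant's own last visit does not fit the Trial status section. Nor does it fit a procedure that puts a pool of clips into random order before scoring. This step is the finding, and it needs no further figures.

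**Step 2. Reproduce the plan's sample size, to have a sound variance for the illustration.** Inputs from Sample size {19}: DOSS 1–7 at 3, 7, 10, 13, 24, 30 and 13%; odds ratio 2; power 90%; 135 subjects; 20% dropout; 168 recruited per group. Two-sided alpha of 0.05 is assumed, since the article states none.

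- Sum of cubed proportions = 0.0466, so 1 − 0.0466 = 0.9534.
- n per group = 6(1.960 + 1.282)² / [(ln 2)² × 0.9534] = 137.6, against the stated 135.
- Power at 135 per group = 89.2%, against 90%.
- 135 / 0.8 = 168.75, against 168.

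The plan's figures reproduce closely, with 135 read as per group.

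**Step 3. Boundary at 75%.** The one-sided alpha of 0.025 is assumed. Cumulative spend = 2[1 − Φ(2.241/√0.75)] = 0.00965, so z = 2.34. An unbiased look therefore crosses in favour of training in about 1% of trials with no true effect.

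**Step 4. Illustration, if site ratings were used and were biased.** Let B be the odds ratio by which unblinded rating favours training when there is no true effect. The range 1.2 to 1.5 is assumed; nothing in the document supports a particular value.

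V = n₁n₂n / [3(n + 1)²] × 0.9534, and P(cross) = 1 − Φ(2.34 − ln B × √V)

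- 101 per arm (0.75 × 135): V = 15.89, √V = 3.986
- 126 per arm (0.75 × 336 / 2): V = 19.86, √V = 4.457

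| B | 101 per arm | 126 per arm |
|---|---|---|
| 1.0 | 1.0% | 1.0% |
| 1.2 | 5.3% | 6.3% |
| 1.3 | 9.8% | 12.1% |
| 1.5 | 23.5% | 29.7% |

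Applying the spending function to two-sided 0.05 instead gives z = 2.26 and slightly higher figures (6.2%, 11.2% and 25.9% with 101 per arm).

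**Step 5. How much rides on this look.** With a true odds ratio of 2 and unbiased scores, P(cross) = 1 − Φ(2.34 − ln 2 × √V), which is 66% with 101 per arm and 77% with 126. Under the plan's own effect size the trial would more likely than not stop here.

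**The case against.** A reader might infer that the trial would be stopped on ratings by staff who know the allocation. The document does not support that. No section says that site-rated DOSS feeds an interim analysis, and none says that the examiner at end of treatment knows the arm. Section {27c} points partly the other way: a blinded investigator judges why a DOSS is missing, and participants are told to keep their allocation to themselves. Section {28b} also calls the 75% analysis the primary one, and the primary outcome is by definition scored blind. So {24b} may simply not have been aligned with {28b}. If no other scores are used, the result is a look that cannot be run, which is an operational failure and not a biased stop.

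This stands, and it limits the point. Sections {22}, {24c} and {25a} make unblinded site ratings possible but do not establish them. The odds ratios in Step 4 illustrate an assumption and do not measure a defect, and the false-superiority risk belongs to the 75% look alone.

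The timing conflict remains. No section provides for blinded scoring before study completion, and none says which DOSS score the interim analyses use.

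**Conclusion.** The conflict between {24b} and {28b} is real. As written, neither interim look has a blinded primary outcome. Either the looks cannot be run, or they would use a site-rated DOSS that may be unblinded and is not the stated primary outcome. This conclusion rests on the wording alone and is firm.

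The possible size of the harm is conditional. If site ratings were used at the 75% look, and if they favoured training by an odds ratio of 1.2 to 1.5, the chance of crossing the boundary under no true effect would rise from about 1% to about 5–24% with 101 per arm, or 6–30% with 126 per arm. That depends on the assumed bias, the assumed one-sided alpha of 0.025 and the assumed number per arm. At the 50% look the risk is a wrongly set sample size. The passages should be reconciled before either look takes place.

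**What to change.** Amend {24b} so that clips are pseudonymized, randomly ordered and scored by the blinded evaluators in batches: one locked before the 50% look, one before the 75% look and one at the end. Each batch should mix all clips then available from baseline, end of treatment and the 6-month follow-up, with both arms together. Otherwise a batch made up mainly of late clips could reveal the time-point, to which {24a} requires evaluators to be blind. Until the trial ends, scores go only to the independent statistician.

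In {28b}, state that both looks use these blinded scores, and that the 75% look applies the same DOSS 0 and imputation rules as the final analysis.

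The cost is small. The same evaluators do the same number of readings, with some added logistics for the staff scientist who prepares the clips. Batching gives up the single random order across the whole trial and allows raters to drift between batches. Because the arms are mixed within each batch, such drift affects both alike.
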